Surgical risk scores such as the European System for Cardiac Operative Risk Evaluation II (EuroSCORE II) and the Society of Thoracic Surgeons (STS) predicted risk of mortality (PROM) score have been validated for surgical interventions. However, they do not contemplate frailty and other comorbidities that impact outcomes in transcatheter procedures. Hence, new scores have been specifically developed to estimate the risk in patients undergoing TAVI (PARTNER, FRANCE 2), although there is no standardized method to evaluate the potential benefit of the procedure. Furthermore, clinical improvement is mostly assessed by the patient's self-reported

change in symptoms, and the clinician's assignment of a New York Heart Association (NYHA) class based on this information. However, it is well established that interobserver agreement of NYHA classification is only around 55%, and there is no consistent method to assign a NYHA class. Therefore, clinical improvement is still essentially a subjective measurement.

In this scenario, CPET, a well-established tool in the preoperative risk assessment of surgical patients, could be a promising tool not only to objectively determine the degree of improvement in functional capacity after TAVI but also to predict the clinical response to TAVI. CPET has been shown to be useful in determining exercise-limiting factors and pathophysiologic mechanisms, and assessing the contribution of cardiovascular, pulmonary and muscular etiology in coexisting disease.

We believe the utility of performing CPET, along with strength tests and frailty scores, in these patients is potentially two-fold. Firstly, identifying which patients have an objective improvement in functional capacity, and have therefore truly benefited from TAVI. Secondly, predicting which group of patients will show this improvement. This could open a door to implementing these strategies in a systematic way to aid in future decisions to proceed with TAVI or not. Identifying patients who are unlikely to benefit from TAVI in their current state could prompt us to offer alternatives that target their specific limitations and needs.

The present study aims to: 1) characterize the mid-term exercise tolerance response to TAVI, and 2) determine the clinical and functional factors that determine the magnitude of this response.

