#### Secondary outcomes:

- To identify clinical and functional pre-TAVI factors that predict improvement in functional capacity after TAVI (i.e., VO2 max increase > 2.5 ml/kg/min).
- To identify clinical, echocardiographic and functional pre-TAVI variables that predict improvement in quality of life.
- Relationship between pre-TAVI CPET parameters and in-hospital complications.
- Relationship between pre-TAVI CPET parameters and complications at 6 weeks.
- Relationship between echocardiographic and CPET parameters after TAVI.
- Relationship between frailty and post-TAVI clinical outcomes.

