### Baseline assessment (T1)

At this time, we will collect demographic variables, clinical history and vitals (see Table 1), and we will perform the preprocedure exercise test. We will perform spirometry prior to the exercise test. The exercise test will be conducted by a physiotherapist and supervised by a physician using a standard incremental cardiopulmonary exercise testing on cycle ergometer (Ergoline 900, Ergoline, Bitz, Germany (CE-0123) and Ergocard Professional, Medisoft, Sorinnes, Belgium (CE-1434)). Based on the patient's anticipated exercise capacity, incremental ramp protocols will be applied with gradual increases in pedal resistance every 3 minutes, maintaining a pedal cadence higher than 50-60 rpm to ensure a consistent workload. The protocols are designed to last between 8 to 12 minutes, ensuring a gradual increase in exertion and preventing sudden spikes in workload that could lead to early fatigue or other complications. The following variables will be obtained for the analysis: oxygen consumption ( $\text{VO}_2$ ) at anaerobic threshold and peak, oxygen pulse ( $\text{VO}_2$  divided by heart rate), respiratory exchange ratio/coefficient (RER) (ratio of  $\text{VCO}_2$  to  $\text{VO}_2$ ),  $\text{VE}/\text{VCO}_2$  slope (ventilatory efficiency, as measured by minute ventilation divided by carbon dioxide production), oxygen uptake efficiency slope, and heart rate at anaerobic threshold (HR at AT).

Based on previous studies, a change in  $\text{VO}_2$  peak equal to or greater than  $2.5 \text{ mL/kg/min}$  between pre and post TAVI will be assumed as a positive response to TAVI in terms of improvement in functional capacity.

Participants will also undergo hand grip strength test (Jamar Hydraulic Hand Dynamometer; Sammons Preston, Bolingbrook, Illinois, USA), and 5 times sit-to-stand test. American Society of Anesthesiologists status, Charlson Comorbidity Index, Barthel Index, STS-PROM score and Euroscore II data will be recorded. Physical activity will be measured by the Yale Physical Activity Survey (YPAS), functional capacity by Duke Activity Status Index questionnaire, frailty by the Essential Frailty Toolset. Quality of life will be measured by Minnesota Living with Heart Failure Questionnaire and Kansas City Cardiomyopathy Questionnaire.

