## 8. Statistics

### 8.1 Sample size

Previous similar studies analyzing exercise testing in patients undergoing percutaneous structural heart interventions have included populations of 11 to 30 patients. Based on our current volume of TAVI patients, we estimate we will include one patient per week in each of the study centers, with a final population of 120 patients in the study.

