### 8.2 Statistical analysis

Categorical data will be expressed as frequency (%). Quantitative variables will be expressed as mean  $\pm$  standard deviation or median and interquartile range (IQR) depending on their distribution. Categorical variables will be analyzed with Fisher's exact test, in case of repeated measures McNemar test will be applied. Continuous variables will be compared with Student's t-test for independent groups and Mann-Whitney U test according to each variable distribution, in case of repeated measures Friedman test will be applied.

For the primary outcome, we will utilize a multiple linear regression analysis to establish the relationship between baseline characteristics and changes in continuous CPET variables following TAVI. To assess the relationship between these baseline characteristics and CPET values and the qualitative secondary outcomes, we will employ a multiple logistic regression analysis. For the secondary outcome, defined as a composite of death, heart failure readmission, and in-hospital complications, we will use a Cox proportional hazards regression model. A p-value of 0.05 will be considered for statistical significance.

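### Where baseline VO2 is a predictor of its own change or of VO2 response, measurement error biases the result towards low baseline VO2 looking favourable, and the protocol does not guard against reading that as differential benefit

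*Protocol*

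**What the plan says.** **Outcome.** The first secondary objective in section 4 is "To identify clinical and functional pre-TAVI factors that predict improvement in functional capacity after TAVI", with improvement defined as a rise in VO2 max of more than 2.5 ml/kg/min. Section 7, Baseline assessment (T1), says that a pre-to-post change in VO2 peak of at least that size "will be assumed as a positive response to TAVI in terms of improvement in functional capacity". In both places the outcome is the raw difference between two tests.

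**Models.** Section 8.2 uses multiple linear regression "to establish the relationship between baseline characteristics and changes in continuous CPET variables following TAVI". For binary outcomes it adds: "To assess the relationship between these baseline characteristics and CPET values and the qualitative secondary outcomes, we will employ a multiple logistic regression analysis". The threshold is given as: "A p-value of 0.05 will be considered for statistical significance".

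**Purpose.** Section 2 wants CPET not only to measure improvement "but also to predict the clinical response to TAVI", and lists as its second use: "Secondly, predicting which group of patients will show this improvement". The section goes on to link this to later decisions on whether to proceed with TAVI.

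**Design.** Section 5 states that there is no control group. Table 1 has one CPET before TAVI and one at six weeks. Section 8.1 plans recruitment "with a final population of 120 patients in the study". The protocol does not mention regression to the mean or test-retest error.

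**The concern.** The observed baseline VO2 is the patient's true value plus the error of that day's test. The change score subtracts the same observed value. A patient who happened to test low at T1 therefore has a low predictor and an inflated change, and a patient who tested high has the reverse. This produces a negative association between baseline and change even when TAVI helps every patient equally.

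With one test per time point and no control group, the trial's own data cannot separate this artefact from a real dependence of benefit on baseline fitness. Other quantities from the same T1 test, such as VO2 at anaerobic threshold or oxygen pulse, can be affected to the extent that they share the error.

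At stake is the study's predictive claim. A finding that less fit patients gain more from TAVI could be partly or wholly an artefact, yet it is the kind of finding that section 2 hopes to use in patient selection.

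**Working it through.** The protocol gives no figure to reproduce here: the 120 patients rest on expected recruitment, with no SD, effect size or reliability.

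**Inputs from the protocol.** n = 120 (8.1); alpha 0.05 (8.2), taken as two-sided; response cut-off 2.5 mL/kg/min (sections 4 and 7).

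**Assumptions not in the protocol.** Observed baseline SD 4 mL/kg/min; test-retest reliability R = 0.95, 0.90 or 0.80; mean true change 1.5 mL/kg/min.

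**Model.** T1 = T + e1 and T2 = T + D + e2, where T is true VO2, D is true change and each error has variance s² = 16(1 − R). Thus s² = 0.8, 1.6 and 3.2.

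**Case A: every patient has the same D.** The covariance of T1 with (T2 − T1) is −s². The variances are 16 and 2s². So the slope is −(1 − R) and the correlation is −√((1 − R)/2).

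**Case B: D has SD 2 and is unrelated to baseline.** The covariance is still −s², but the variance of change is 2s² + 4. The correlation is −s² / (4√(2s² + 4)); for R = 0.90 this is −1.6 / (4√7.2) = −0.15.

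The linear rate of false significance follows approximately from Fisher's z: atanh|r| × √117 compared with 1.96. For case A at R = 0.90, atanh(0.224) × 10.82 = 2.46, so the rate is P(Z > 1.96 − 2.46) = 69%. Simulation agrees. The logistic rates (response = change of at least 2.5) come from simulation.

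| | R = 0.95 | R = 0.90 | R = 0.80 |
|---|---|---|---|
| A: correlation | −0.16 | −0.22 | −0.32 |
| A: falsely significant, linear | 41% | 69% | 95% |
| A: falsely significant, logistic | 23% | 45% | 77% |
| B: correlation | −0.08 | −0.15 | −0.25 |
| B: falsely significant, linear | 15% | 38% | 78% |
| B: falsely significant, logistic | 9–11% | 22–24% | 52–58% |

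The logistic ranges in case B are the spread over several simulation runs. In case A the logistic rates also move with the mean change: at 1.0 and 2.5 mL/kg/min they are 16–27%, 39–50% and 71–80%. With negligible measurement error the linear rate returns to 5%.

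**Two common remedies, checked in the same model.**

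- *Oldham's method* (change against the mean of T1 and T2). It holds its 5% level in case A. In case B the covariance of the mean with change is Var(D)/2 = 2, which is not zero. At R = 0.90 the correlation is 2 / √(16.2 × 7.2) = +0.19, and false significance is about 63%, 52% and 42% for the three values of R. Hypothesis 2 in section 3 expects response to vary, so case B is the relevant one.
- *Forcing T1 VO2 into every model.* Take a predictor correlated 0.5 with true VO2, as frailty or grip strength might be, with identical true change. Without T1 VO2 its false-positive rate is 5%. With T1 VO2 at R = 0.90, its correlation with T1 is 0.5 × √0.90 = 0.474, and the partial correlation with change is 0.474 × 0.224 / √((1 − 0.225)(1 − 0.05)) = 0.12. The false-positive rates are about 16%, 27% and 45%.

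**The case against.** The strongest reply is that section 8.2 gives no covariate list, so baseline VO2 is never named as a predictor of its own change, and covariate handling is commonly left to an SAP. The first part is true: the covariate is inferred from the mention of CPET values in 8.2, the functional pre-TAVI factors in section 4 and the predictive aim in section 2. Those passages leave little room for a reading that excludes it. The choice of change as outcome, baseline CPET as predictor and the type of model is made in the protocol itself.

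A second reply is that including baseline as a covariate is ordinary practice. That stands. A reader might infer that any model containing T1 VO2 is wrong, and the argument does not support this. The error lies in interpreting the T1 coefficient as differential benefit.

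A reader might also infer that the plan is bound to produce a significant spurious predictor. It is not. In the logistic model at R = 0.95, baseline VO2 is non-significant in most simulated trials. Nor is every use of the logistic sentence affected: it also covers complications, where T1 CPET is a legitimate predictor and no error is shared with the outcome.

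**Conclusion.** The point holds for models of VO2 change and VO2 response in which baseline VO2, or a T1 CPET measure sharing its error, is a predictor. The direction of the bias is certain given any measurement error. Its size depends on a reliability that the protocol does not state. Over R from 0.95 to 0.80, false significance runs from about 41% to 95% (linear) and 23% to 77% (logistic) if true change is identical. If true change varies with SD 2 independently of baseline, it runs from about 15% to 78% (linear) and from about 10% to somewhat over 50% (logistic). These figures rest on n = 120 with complete data, baseline SD 4, normal errors and baseline VO2 as the only predictor; the effect on other T1 measures is not quantified here. The documents do not support the stronger claim that any low-baseline finding would be pure artefact, since a real dependence on baseline may also exist. The plan as written cannot tell the two apart.

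**What to change.** Add to section 8.2 that, in models of VO2 change or VO2 response, the coefficient of T1 VO2 and of T1 CPET measures sharing its error will not be read as evidence of who benefits, unless it is corrected for test-retest error using a stated reliability, with its source and a sensitivity range. Say that this does not apply to the complication outcomes.

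Do not use Oldham's method as the correction, because it is invalid when true change varies between patients. Do not require T1 VO2 in the models for all other predictors. If it is included, report those predictors both with and without it, since adjusting for a noisy baseline can create spurious associations for correlated predictors such as frailty or grip strength.

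The cost is analysis wording, plus finding a defensible reliability figure if baseline dependence is to be studied. The downside is that baseline VO2 cannot be claimed as a predictor of response from the uncorrected model.

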To our knowledge, the potential functional benefit of TAVI has not been well explored using cardiopulmonary exercise testing (CPET), a method considered the gold standard for measuring functional capacity. A significant increase in exercise time, oxygen consumption and ventilatory anaerobic threshold (by CPET) has been shown in a small sample of 11 patients with heart failure, 6 months after percutaneous mitral valve repair. Another study including both patients who underwent SAVR and TAVI, did not observe an improvement in VO2 max after 9 months of the procedure. A preoperative transvalvular gradient < 40mmHg, high preoperative Brain Natriuretic Peptide, previous beta-blocker treatment and patients with a pacemaker were associated with a lower relative change in VO2 max. A recent small study published in 2020 by a group from Switzerland, explored the short-term changes in functional capacity in 30 patients after TAVI. They did not use CPET but electrical cardiometry and near-infrared spectroscopy and they showed improved median workload, cardiac index and cerebral and muscle tissue oximetry at 5 days compared to baseline. No data were reported about the potential improvement in aerobic capacity.

On the other hand, most patients who undergo TAVI are elderly, and characterized by a high frailty degree, multiple comorbidities, and muscular deconditioning, which involves not only sarcopenia but also mitochondrial dysfunction, all well described in the heart failure population. Our premise is that there are multiple factors that contribute to their limitation in functional capacity beyond the aortic stenosis itself. This makes it challenging to determine which patients will truly benefit from TAVI and those whose symptoms will partially or not improve despite eliminating the obstruction.

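### The response-prediction models put no limit on predictors (about 55 baseline variables are collected) in 120 patients, so overfitting is likely unless the candidate set is cut in advance or the fit is penalised

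*Protocol*

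**What the plan says.** Prediction of response is one of the study's two aims (section 2), its second hypothesis (section 3) and its first secondary outcome (section 4). Section 2 says of the intended use: "This could open a door to implementing these strategies in a systematic way to aid in future decisions to proceed with TAVI or not".

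Section 8.2 assigns multiple linear regression to the relation between baseline characteristics and change in continuous CPET variables. For the binary outcomes it reads: "To assess the relationship between these baseline characteristics and CPET values and the qualitative secondary outcomes", "we will employ a multiple logistic regression analysis". The criterion is "A p-value of 0.05 will be considered for statistical significance". No number or list of predictors is given, and neither shrinkage nor validation is mentioned.

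Section 8.1 ends "with a final population of 120 patients in the study". Its basis is recruitment ("we estimate we will include one patient per week in each of the study centers") and precedent: earlier studies "have included populations of 11 to 30 patients". No response rate, effect size, standard deviation or predictor count enters.

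**The concern.** A regression model with many candidate predictors and few events fits noise. It then looks better in the data that produced it than in new patients, and some of its significant predictors are chance findings. Section 8.2 combines four features that invite this: an open predictor set, regression without a stated penalty, a per-variable p-value criterion, and a sample size not chosen for prediction. The binary responder outcome makes it worse, because cutting a continuous change at 2.5 mL/kg/min discards information.

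The aim is to say which patients are unlikely to gain functional capacity from TAVI. A predictor list or apparent accuracy that does not carry over to new patients would mislead on that question.

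**Working it through.** **The plan's own figure.** N = 120 cannot be reproduced. Section 8.1 gives no formula, and one patient per week per centre cannot be multiplied out because neither the number of centres nor the recruitment period is stated.

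**Step 1: variables collected before TAVI** (section 7, Baseline assessment, and Table 1)

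| Group | Count |
|---|---|
| Demographics | 3 |
| Charlson, ASA, EuroSCORE II, STS-PROM, Barthel | 5 |
| Frailty | 1 |
| NYHA, device, AF/flutter, COPD, diuretic | 5 |
| Heart failure drugs | 7 |
| Rate drugs | 3 |
| Vitals | 4 |
| Echocardiography | 5 |
| Blood tests | 10 |
| MLHFQ, KCCQ-12, YPAS | 3 |
| Sit-to-stand, grip strength | 2 |
| CPET | 7 |
| **Total** | **55** |

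The Duke questionnaire, named in section 7 but not in Table 1, would make 56. Collapsing each of the two drug lists to one variable gives 56 − 6 − 2 = 48; splitting paired measures gives about 60.

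**Step 2: events per collected variable.** The smaller outcome group cannot exceed 60 of 120, so the ceiling is 60/55 = 1.09. This needs no assumption about the response rate.

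**Step 3: plausible number of responders (assumed).** The protocol gives no mean change or SD. With a normal change, responders = 120 × [1 − Φ((2.5 − mean)/SD)]:

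| Mean change | SD | Responders |
|---|---|---|
| 0 | 2.5 | 120 × 0.159 = 19 |
| 0 | 3 | 120 × 0.202 = 24 |
| 1 | 2.5 | 120 × 0.274 = 33 |
| 1.5 | 3 | 120 × 0.369 = 44 |

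Widening to means of 0 to 2 and SDs of 2 to 3.5 gives 13 to 53. For 20 to 45 responders, events per collected variable run from 20/55 = 0.36 to 45/55 = 0.82. At the usual 10 events per parameter, 20/10 = 2 and 45/10 = 4.5, so about 2 to 4 unpenalised predictors are supportable. Section 8.1 states no allowance for patients without a second CPET. An assumed 20% loss leaves 96 patients and, over the wider range, 10 to 43 responders.

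**Step 4: worst cases, if all 55 variables are entered or tested and none has any effect**

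- Linear model with all 55: expected R² = 55/119 = 0.46.
- All 55 tested at 0.05: 55 × 0.05 = 2.75 false positives expected. The chance of at least one is 1 − 0.95^55 = 0.94 if the tests are independent.
- Simulated noise (100 runs per setting, independent predictors): a 55-variable logistic model separates completely in 99%, 91% and 40% of runs at 20, 30 and 45 responders.
- Simulated noise, screening at p < 0.05 before the multiple logistic model: mean apparent AUC of 0.67 to 0.76 (independent predictors or correlation 0.3), against a true 0.50.
- For comparison, 3 prespecified noise predictors give an apparent AUC of 0.59 to 0.61.

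**Step 5: sample size for limited shrinkage.** With n = P / [(S − 1) ln(1 − R²/S)], S = 0.9, and an assumed R² of 15% to 30% of its maximum, 5 parameters need about 180 to 480 patients and 3 parameters about 107 to 288. So 120 is tight even for a small unpenalised responder model.

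**The case against.** The strongest reply is that section 8.2 names a model family and a threshold, and nothing more. It does not say that all variables enter, that univariable screening will be used, or that shrinkage and validation are ruled out. Such details are commonly left to a statistical analysis plan, and one may exist. Table 1 is a data-collection schedule, not a list of predictors. All of this stands. A reader might infer that the protocol commits to a 55-variable model with a null R² of 0.46 and a 94% chance of a false predictor. The document does not support that: those figures need all 55 to be entered or tested. The 94% also needs independence, which near-duplicates such as hemoglobin and hematocrit, or creatinine and filtration rate, contradict.

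Three further points stand.

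- A continuous model is already planned for the primary outcome, so the plan does not rest on the responder cut-off alone.
- The responder count is assumed. The mixed surgical and transcatheter study cited in section 2, which "did not observe an improvement in" VO2 max, was assessed at 9 months rather than 6 weeks. No mean improvement makes few responders possible, not certain.
- The clinical use is put tentatively, and section 7 says that no clinical decisions will follow from the assessments.

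What the reply does not remove is that the protocol itself states the method, the threshold and N for an aim it words as prediction. A later plan can shorten the list or add a penalty, but under this protocol it starts from 120 patients. At that size, the choice among some 55 variables has to be made before the data are seen.

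**Conclusion.** The concern holds in conditional form: the response model is likely to be overfitted unless the candidate set is cut in advance or the fit is penalised. That it will be overfitted, or will fail in new patients, is a stronger reading that the document does not support.

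The firm figure is the ceiling of about 1.1 events per collected variable, which depends only on N = 120 and the count of about 55 (48 to 60 depending on how variables are split). The 2 to 4 supportable predictors rest on the assumed 20 to 45 responders and on the 10-events rule of thumb. The 0.46, the 94% and the simulation results with 55 variables are worst cases. This is a worthwhile and cheap improvement to the analysis, not a flaw that invalidates the study.

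**What to change.** In section 8.2:

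- Keep the continuous model already planned as the lead predictor analysis. Always include T1 VO2 peak as a covariate, because the change contains the baseline value, and use at most about 10 predictors chosen in advance on clinical grounds. With 10 predictors plus T1 VO2 peak, R² expected from noise alone falls to 11/119 = 0.09.
- Treat the responder model (change of 2.5 mL/kg/min) as supportive. Fit it either with penalisation (ridge, LASSO or Firth) on that short list, or with no more than about 3 to 4 prespecified unpenalised predictors, and fewer if responders are near 20. Ten predictors would have only 2 to 4.5 events each (20/10 to 45/10), so penalisation mitigates the problem but does not remove it.
- Report bootstrap optimism-corrected R², c-statistic and calibration, repeating any selection step in each resample.
- Describe the model as exploratory until externally validated.

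Section 4 (above 2.5) and section 7 (2.5 or more) should also be reconciled on the cut-off.

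The cost is revised wording and some programming; no patients or visits are added. The downside is that fewer predictors can be claimed and the reported performance will be less favourable.
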